**Figure 3 F3:**
[figure not shown]
Photograph of a patient using Mobility Rehab with a PT during a therapy session.

The Mobility Rehab system includes a tablet (to visualize gait measures) and five Opal sensors (APDM, Portland, Oregon, USA), that are placed on both wrists and feet and at the sternum level. The wireless sensors are easy to attach with Velcro straps and highly portable, enabling assessment to be performed in almost any environment. Figure 4 shows a screen-shot of the display.

**Figure 4 F4:**
[figure not shown]
Mobility Rehab interface and visualization of gait metrics while walking. Example of biofeedback visualization of arm range of motion while walking. Bars indicate left and right arm range of motion during straight walking (blue) and 180° turns (orange).

The user can see metrics for both the right and left sides (top panel and bottom panel) in which each bar represents the value of one step/stride and the gray area represents the normative values. In addition, intervals can be set as target (blue lines) to reach while walking. Each time a new step/stride is added, a new bar is appended and appears on the graph. The system will record each metric used for each session, length of the session, and if the training was on treadmill or overground. In addition, the system provides therapists and patients with online reports that convey patients' performance during the training session and a comparison to baseline gait data.

### Adverse Events

Adverse events during the intervention period are reported to the research group by the training therapists. The investigators report adverse events and unanticipated problems in accord with the policies of the OHSU Institutional Review Board. If trends in adverse events are noted, preventive measures will be implemented and participants will receive advice on avoiding such events.

### Outcomes and Procedures

The primary outcome measure is the subjects' perception of balance confidence as the patient-related-outcome (common in pragmatic trials). Subjects' perception of balance is measured with the Activities-specific Balance Confidence scale (ABC). The ABC consists of 16 questions about subjects' confidence in not losing balance while engaged in daily-life activities, such as picking something up from the floor, riding an escalator, and walking across a parking lot. Subjects respond on a scale from 0 to 100%, representing the confidence they have in their balance when doing or imagine if they did these tasks. ABC score above 50 and lower than 80 indicates a moderate level of functioning characteristics of elders in retirement homes and persons with chronic health conditions (23). The ABC has been shown to reflect the activities in which people actually participate that involve walking (24).

The secondary outcome measure is gait speed, as it has been reported as the 6th vital sign and predictive of mortality (25). Gait speed is measured during two instrumented, 2-min walks. Participants are invited to walk back and forth along a 9-meter long corridor. The first walk bout is performed at the individual's casual walking pace and the second is performed at a pace the individual considers to be faster than their casual pace. The Mobility Lab software is used to collect the walking data and calculate gait speed and additional spatiotemporal gait parameters (i.e., step time asymmetry, foot clearance, arm swing, trunk lateral range, and foot strike angle), which will be reported as exploratory outcomes in this trial (26).

### Sample Size and Power Analysis

#### ABC Scale

We anticipate most of our subjects will score in the 50–80 range on the ABC scale at baseline, although we will not exclude those with scores lower than 50. We extracted means and standard deviations (SDs) from published studies involving both community dwelling and home-care facility based older adults (23). Based on these studies, we assume our subjects will have an average score of 60 at baseline with a SD in the 11–20 range. Furthermore, a 12-point change in the scale has been reported to be clinically relevant (27). We anticipate that both the standard therapy and therapist-assisted feedback treatment groups will improve, but the feedback group will score at least 12 points higher on ABC scale at post-assessment. Thus, we anticipate group effect sizes between 0.6 and 1.2 SD for the current study. Type 1 error for the sole primary outcome was set to 0.05. Because we propose to randomize PTs rather than patients, there is clustering inherent in the study design (i.e., cluster-randomization). We account for clustering by computing power based on the effective sample size rather than the actual sample size (28). The effective sample size (ESS = m ^*^ (number of therapists)/DEFF) is based on the design effect (DEFF = 1 + (m – 1) ^*^ ICC), where ICC = intra-cluster (therapist) correlation and m = 50 is the anticipated # patients/therapist. We examined power to detect anticipated changes for a range of ICC between 0.002 and 0.010 [are based on values reported by Killip et al. (28)]. With 200 subjects equally allocated to each of the four therapists (two of which are randomized to therapist-assisted feedback group), the trial is adequately powered (84.3–96.1%) to detect effect sizes between 0.9 and 1.2 SD when ICC = 0,002; effect size of 1.1 SD is detectable with 82.6–91.1% power when ICC is higher (0.10).

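### The adequate-power statement covers only 0.9 to 1.2 SD, while the 12-point target with the assumed SD of 11 to 20 is 0.60 to 1.09 SD; power for 12 points is below 80% over most of that SD range

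*Protocol article*

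**What the plan says.** All of the relevant text is in the protocol article, Sample Size and Power Analysis, ABC Scale.

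- Spread: "we assume our subjects will have an average score of 60 at baseline with a SD in the 11–20 range".
- Target: the section cites a 12-point change as clinically relevant and expects that "the feedback group will score at least 12 points higher on ABC scale at post-assessment".
- Resulting effect size: "Thus, we anticipate group effect sizes between 0.6 and 1.2 SD for the current study".
- Error rate and design: "Type 1 error for the sole primary outcome was set to 0.05"; there are four therapists, two per arm, and "m = 50 is the anticipated # patients/therapist". Clustering is handled through an effective sample size and a design effect, over ICCs from 0.002 to 0.010.
- Conclusion: "the trial is adequately powered (84.3–96.1%) to detect effect sizes between 0.9 and 1.2 SD when ICC = 0,002". A further clause gives power for 1.1 SD at a higher ICC.

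No power is given for any effect below 0.9 SD.

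**The concern.** The section derives one range of effects (0.6 to 1.2 SD) and then reports power for the upper half of it only (0.9 to 1.2 SD). The two ends of the derived range also do not come from the same inputs. The lower end is exactly 12 points over the largest assumed SD, but the upper end is not 12 points over the smallest.

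The unreported half is where a 12-point difference lies if the SD is above 13.3, and those values make up most of the assumed range. A reader who wants to know how likely the trial is to detect the difference it calls clinically relevant has no figure for those SDs. If the SD turned out to be 15 or 20 and the result were not significant, the published adequacy statement would invite the reader to take it as stronger evidence against a 12-point benefit than the design can give.

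**Working it through.** **Inputs (ABC Scale section).** Difference 12 points; SD 11 to 20; m = 50 patients per therapist; 4 therapists, 2 per arm; 200 patients; type 1 error 0.05; ICC 0.002 to 0.010. ICC 0.005 is added as a middle value; the Gait Speed section uses it. The article does not say whether the test is two-sided and does not give the degrees of freedom; both are inferred in step 2. No allowance for dropout is needed, because Recruitment and Screening continues enrolment until 200 people have completed both assessments.

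**Step 1: effect size implied by 12 points.**
- SD 20: 12/20 = 0.60 SD
- SD 11: 12/11 = 1.09 SD
- For 1.2 SD: 12/1.2 = SD 10, or 1.2 × 11 = 13.2 points
- For 0.9 SD: 12/0.9 = SD 13.3

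**Step 2: reproduce the printed power.** DEFF = 1 + (50 − 1) × ICC; ESS = 200/DEFF; noncentrality = d/√(4/ESS) = d × √ESS/2. Power is taken from the noncentral t distribution with 4 − 2 = 2 degrees of freedom, two-sided 0.05, critical value 4.303.

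At ICC 0.002, DEFF = 1 + 49 × 0.002 = 1.098, ESS = 200/1.098 = 182.1 and √182.1/2 = 6.748.
- d = 0.9: noncentrality 6.07, power 84.3% (printed: 84.3%)
- d = 1.2: noncentrality 8.10, power 96.1% (printed: 96.1%)

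A simulation of four therapist means with 400,000 runs gave 84.2% and 96.1%. The alternatives do not match. A normal approximation, or a t-test with ESS − 2 degrees of freedom, gives about 100% at both effects. A one-sided test on 2 degrees of freedom gives 97.3% and 99.8%, and 3 degrees of freedom gives 97.0% and 99.9%.

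**Step 3: the same method for 12 points across the assumed SDs.** DEFF is 1.098, 1.245 and 1.49 at ICC 0.002, 0.005 and 0.010; ESS is 182.1, 160.6 and 134.2.

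| SD | 12 points in SD units | ICC 0.002 | ICC 0.005 | ICC 0.010 |
|---|---|---|---|---|
| 11 | 1.09 | 93% | 91% | 86% |
| 13.3 | 0.90 | 84% | 81% | 75% |
| 15 | 0.80 | 77% | 73% | 67% |
| 20 | 0.60 | 57% | 53% | 47% |

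**Step 4: where power crosses 80%.** Solving the same formula for 80% power gives d = 0.838, 0.892 and 0.976 at the three ICCs. The largest SD at which 12 points has 80% power is therefore 12/0.838 = 14.3, 12/0.892 = 13.5 and 12/0.976 = 12.3. The share of the 11 to 20 range above those limits is (20 − 14.3)/9 = 63%, (20 − 13.5)/9 = 72% and (20 − 12.3)/9 = 86%.

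**The case against.** The strongest defence is that the sentence is literally true. It claims adequate power for 0.9 to 1.2 SD, both printed figures reproduce, and the section never says that 12 points is covered at every SD from 11 to 20. That stands. A reader might infer that the power was miscalculated, or that the article asserts adequate power for 12 points throughout, and the text supports neither reading. The fault is that the section sets a target, derives a range from it, and reports on only half of that range.

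Second, 12 points is stated as a minimum, so 1.2 SD is not impossible: 13.2 points at SD 11 would give it. This also stands. The upper limit is unsupported rather than proven wrong, because no larger difference is named.

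Third, a reader might take the 47 to 57% as the power for the whole 0.60 to 1.09 SD range, or place the start of the shortfall at SD 13.3. Neither is right. The 47 to 57% applies only at SD 20. At SD 13.3 power is still 84% and 81% at the two lower ICCs, and the shortfall begins at the limits in step 4.

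Fourth, the 2 degrees of freedom are inferred. With patient-level degrees of freedom, power at 0.60 SD would be 93 to 98%, but that method does not reproduce the article's figures.

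Fifth, the SD of 11 to 20 is given for baseline scores, and covariate adjustment could reduce the residual SD. That is possible, but the power calculation uses no such reduction, and Statistical Analysis names only age, gender and pathology as examples of the adjusting characteristics.

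**Conclusion.** The point holds as an incomplete and loosely derived power statement. By the method that reproduces the article's own figures, power for its 12-point target is 86 to 93% at SD 11, 67 to 77% at SD 15 and 47 to 57% at SD 20. It is below 80% for roughly 63 to 86% of the assumed SD range, depending on the ICC.

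This rests on a two-sided 0.05 test with 2 degrees of freedom (inferred), equal clusters of 50, ICCs within the stated 0.002 to 0.010, and the assumed baseline SD applying to the post-assessment comparison with no gain from covariates. Severity is should-fix: the sole primary outcome is affected, but the remedy is a restatement, and the design, endpoint and analysis do not change.

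**What to change.** In the ABC Scale section:

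1. Give the effect range for a 12-point difference as 0.60 to 1.09 SD, or state and justify the larger difference that leads to 1.2 SD.
2. Report power for 12 points at SD 11, 15 and 20 for ICC 0.002, 0.005 and 0.010, as in the table above.
3. Limit the adequacy statement to SDs of no more than about 14.3, 13.5 and 12.3 at those ICCs.
4. State the degrees of freedom and sidedness used. If a smaller residual SD is expected from covariate adjustment, state it and give the power on that SD.

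The cost is a few restated figures. No extra patients are needed, but the stated power becomes less favourable.

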#### Gait Speed

Under similar assumptions for ICC, we computed power to detect changes assuming a sample size of 200 allocated as noted above. Evaluated group differences for gait speed between 0.06 and 0.12 (29). Since gait speed is not the primary outcome, we did not control for multiple comparisons, and left type 1 error equal to 0.05. Power is ≥85.7% to detect at least 0.12 m/s difference when ICC is at or below 0.005, and ≥80.5% to detect at least 0.12 m/s difference when ICC is 0.01.

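### The stated 82.6–91.1% power for 1.1 SD at an ICC of 0.10 is wrong: the calculation behind the plan's other power figures gives 42%

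*Protocol article*

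**What the plan says.** The ABC Scale part of the section Sample Size and Power Analysis sets out the calculation as follows.

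- Error rate: "Type 1 error for the sole primary outcome was set to 0.05".
- Design: "With 200 subjects equally allocated to each of the four therapists (two of which are randomized to therapist-assisted feedback group"), and "m = 50 is the anticipated # patients/therapist".
- Clustering is handled by an effective sample size, "ESS = m ^*^ (number of therapists)/DEFF", with a design effect of 1 + (m – 1) × ICC.
- ICCs considered: "We examined power to detect anticipated changes for a range of ICC between 0.002 and 0.010".
- Result at the low end: "the trial is adequately powered (84.3–96.1%) to detect effect sizes between 0.9 and 1.2 SD when ICC = 0,002".
- Result at a higher ICC: "effect size of 1.1 SD is detectable with 82.6–91.1% power when ICC is higher (0.10").

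The Gait Speed part, which relies on similar ICC assumptions, gives power at ICCs of 0.005 and 0.01 and none higher.

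**The concern.** Two faults are visible before any calculation. The last ABC statement uses an ICC ten times the upper end of the range said to have been examined. It also attaches a range of powers to one effect size at one ICC, although sample size, cluster size and alpha are all fixed.

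With four therapists, the ICC is the assumption on which power depends most, and this is the only ABC power statement for an ICC above 0.002. As printed, it tells the reader that the trial keeps more than 80% power at a therapist ICC of 0.10. The document gives no ICC estimate for this clinic. However, the therapists design their own treatment plans and were chosen to differ in experience (under 5 versus over 10 years), so a value above 0.010 cannot be dismissed. Anyone interpreting a null result would be misled about what the trial could detect.

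**Working it through.** **Inputs (ABC Scale section).** 200 patients; 4 therapists, 2 per arm; m = 50 per therapist; alpha 0.05. Sidedness is not stated; two-sided is taken because it reproduces the plan's figures.

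**Formulas.**
- DEFF = 1 + 49 × ICC
- ESS = 200 / DEFF
- noncentrality = d × √(ESS/4), where d is the effect in SDs
- power from the noncentral t with 4 – 2 = 2 df, critical value 4.303

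The article does not name the degrees of freedom, so the method is identified by whether it returns the printed figures.

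**Step 1: reproduce the plan's figures at ICC 0.002.** DEFF = 1 + 49 × 0.002 = 1.098; ESS = 200/1.098 = 182.1; √(182.1/4) = 6.748.
- d = 0.9: noncentrality 6.07, power 84.3% (stated 84.3%)
- d = 1.2: noncentrality 8.10, power 96.1% (stated 96.1%)

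A simulated t-test on the four therapist means gives the same two values. Alternatives fail: at 0.9 SD, a t-test with ESS – 2 df or a normal approximation on the ESS gives about 100%, a one-sided 2-df test gives 97.3%, and a 3-df test gives 97.0%.

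**Step 2: cross-check on gait speed.** No SD is given, so it has to be fitted. The two stated powers for 0.12 m/s (85.7% at ICC 0.005, 80.5% at ICC 0.01) both imply a standardised effect of about 0.98, that is, an SD of 0.12/0.98 ≈ 0.122 m/s. Two figures with one fitted value amount to one consistency check, and the 2-df method passes it.

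**Step 3: the disputed statement.** At ICC 0.10, DEFF = 1 + 49 × 0.10 = 5.9; ESS = 200/5.9 = 33.9; noncentrality = 1.1 × √(33.9/4) = 3.20. Power is 42.4% (simulation 42.3%), against the stated 82.6–91.1%. The shortfall is 82.6 – 42.4 = 40.2 to 91.1 – 42.4 = 48.7 percentage points.

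Other effects at ICC 0.10: 0.6 SD, 18%; 0.9 SD, 32%; 1.2 SD, 47.6%. Power of 80% would need 1.94 SD, or 1.94 × 11 = 21 to 1.94 × 20 = 39 ABC points over the plan's SD range of 11 to 20.

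**Step 4: where the printed figures come from.** Power at 1.1 SD by ICC:

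| ICC | DEFF | ESS | Power |
|---|---|---|---|
| 0.002 | 1.098 | 182.1 | 93.5% |
| 0.005 | 1.245 | 160.6 | 91.1% |
| 0.010 | 1.490 | 134.2 | 86.9% |
| 0.015 | 1.735 | 115.3 | 82.6% |
| 0.05 | 3.450 | 58.0 | 60% |
| 0.10 | 5.900 | 33.9 | 42% |

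The printed endpoints match ICC 0.005 and 0.015. A range over effect sizes at ICC 0.010 does not fit: 1.0 SD gives 81.5% and 1.2 SD gives 91.0%.

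**The case against.** The strongest reply is that the error lies in the ICC and the powers themselves are sound. The value 0.10 appears nowhere else, the examined range stops at 0.010, and the gait-speed paragraph stops at 0.01. On that reading 0.10 is a decimal slip, power at 0.010 is an adequate 86.9%, and 42% describes a scenario the authors never meant. As an account of how the error arose, this is likely right, and the 42% should be read as the correction of the printed claim. It does not rescue the sentence: changing 0.10 to 0.010 leaves a range where only one value is possible, and the lower endpoint belongs to an ICC outside the stated range.

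A second reply is that the 2-df test is inferred, while the article says only that power rests on the effective sample size. A t-test on the ESS with ESS – 2 df gives 87.4% at ICC 0.10, inside the printed range. But the same test gives about 100% where the plan states 84.3% and 96.1%, so it did not produce those figures, and it too would give one value.

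It is also fair to say that nothing in the document supports an ICC near 0.10, and that showing power at 0.05 and 0.10 goes beyond the minimum correction. Whether the examined range is too narrow is a separate design question.

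**Conclusion.** The concern holds. As printed, the statement contradicts the examined ICC range, gives a range where one value is possible, and overstates power at ICC 0.10 by 40 to 49 percentage points: 42.4% instead of 82.6–91.1%. The 42.4% assumes a two-sided 5% test on 2 df with 50 patients per therapist, which is the calculation that returns the plan's ICC 0.002 figures to the decimal. If 0.010 was meant, power at 1.1 SD is adequate at 86.9%, but the sentence still needs correcting. Because it belongs to the power statement for the primary outcome, it must be put right under either reading.

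**What to change.** Replace the sentence with power at 1.1 SD for each named ICC: 93.5% (0.002), 91.1% (0.005), 86.9% (0.010), 82.6% (0.015), 60% (0.05) and 42% (0.10). Make the ICC range said to have been examined agree with the ICCs reported, and state that the test is two-sided on 2 df so that the figures can be reproduced. At the least, say which ICCs 82.6% and 91.1% refer to and extend the examined range to 0.015; if 0.10 was really intended, report 42%. The cost is restated figures only, with no change to sample size, design or analysis.

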#### Gait Speed

Under similar assumptions for ICC, we computed power to detect changes assuming a sample size of 200 allocated as noted above. Evaluated group differences for gait speed between 0.06 and 0.12 (29). Since gait speed is not the primary outcome, we did not control for multiple comparisons, and left type 1 error equal to 0.05. Power is ≥85.7% to detect at least 0.12 m/s difference when ICC is at or below 0.005, and ≥80.5% to detect at least 0.12 m/s difference when ICC is 0.01.

### Statistical Analysis

The analysis will adopt the intent-to-treat strategy. We will estimate and evaluate the difference in the post-assessment ABC between the two treatment groups, adjusting for participants' baseline characteristics (i.e., age, gender, and pathology). Since the outcome of interest is measured at the individual patient level, but PTs are the unit of randomization (i.e., PTs are assigned to either provide feedback in addition to usual care or not), we will fit a linear mixed effects model with post-assessment ABC as the dependent variable; fixed independent effects will be treatment group (therapist-assisted feedback therapy vs. standard therapy) and a random effect term to account for PT variability. The same model will be used to investigate changes on gait speed, our secondary outcome measure. Additionally, we will carry out a sensitivity analysis for those that complete at least 9 (out of 12) sessions to identify whether or not a certain number of sessions influences the observed effects, if any.

An exploratory analysis is proposed including estimating post-intervention differences in other gait metrics collected by the blinded assessor. These secondary gait outcomes will be fit with models similar to the primary outcome measure.

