## Methods and Analysis

### Trial Design

The study is a single-site, pragmatic, controlled clinical trial in older people with gait disturbances. The trial compares standard-of-care gait training by PTs with therapist-assisted feedback therapy using Mobility Rehab in the same clinic. Participants scheduled at the physical therapy clinic for gait training are assigned to one of the four PTs, and that will determine, if eligible, their group assignment for the duration of their outpatient therapy. Assessments occur at baseline (pre) before intervention starts and immediately after the last session of intervention (post). The trial design is illustrated in Figure 1. This protocol paper follows the SPIRIT (Standard Protocol Items: Recommendations for Interventional Trials) 2013 statement and guidelines (22). SPIRIT template for the schedule of enrollment, interventions, and assessments is presented in Figure 2.

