### Assignment and Blinding

A PT aide who schedules patient appointments assigns each prescreened patient to one of the four PTs who deliver the interventions, depending their open schedule. If a patient is eligible, then he/she undergoes the intervention with the assigned PT. Thus, although the patients are not randomly assigned to each group, this approach was practical for the clinic and avoided selective enrollment assignment since the PT aide assigns an upcoming patient to a PT according to schedule availability without regard to diagnosis, age, or sex. To prevent performance bias, the four treating PTs were distributed into two groups: two PTs provide traditional physical therapy for 100 participants, while the two other PTs provide feedback-based therapy for the other 100 participants. We do not anticipate any selection bias and we do expect equal number of subjects to be assigned to each of the four PTs. Furthermore, information that could introduce bias are withheld from subjects in both groups, i.e., their informed consent does not mention efficacy of feedback-based therapy. To prevent bias due to varying levels of PTs experience, one very experienced PT (>10 years working with patients) and one less experienced PT (<5 years working experience) were assigned to use Mobility Rehab and a similar stratification of experienced and inexperienced PTs were assigned to not use Mobility Rehab. Detection bias is avoided by blinding the PT assistants who administer the pre- and post-assessments and by blinding the investigators and statisticians at OHSU who are analyzing the results regarding subjects' group assignment.

Although we are not assessing blinding by the outcome assessors, the following measures are implemented to avoid assessors from gaining impressions/information about treatment assignment: assessors are based in a different building from the one where the interventions are carried out and, therefore, they do not see patients during rehabilitation sessions and; participants are asked to refrain from mentioning their group allocation to assessors.

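### The outcome models adjust for age, gender and pathology but leave out the baseline value of the outcome (ABC, gait speed), which loses precision and leaves starting differences between arms uncorrected

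*Protocol article*

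**What the plan says.** All references are to the protocol article.

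- **Primary model (Statistical Analysis).** "we will fit a linear mixed effects model with post-assessment ABC as the dependent variable". The terms are then named: "fixed independent effects will be treatment group (therapist-assisted feedback therapy vs. standard therapy) and a random effect term to account for PT variability". The sentence before gives the adjustment, for "baseline characteristics (i.e., age, gender, and pathology").
- **Other outcomes (Statistical Analysis).** "The same model will be used to investigate changes on gait speed, our secondary outcome measure". The exploratory gait metrics get models similar to the primary one.
- **Baseline data (Trial Design).** "Assessments occur at baseline (pre) before intervention starts and immediately after the last session of intervention (post"). Outcomes and Procedures describes ABC and the instrumented walks as the measures taken.
- **Allocation (Assignment and Blinding).** The article states that "although the patients are not randomly assigned to each group"; an aide books each patient with whichever therapist has an opening. Four therapists were randomised, two to each arm.

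No change-score or repeated-measures model appears anywhere in the article.

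**The concern.** The covariate list is introduced by i.e., which makes it complete rather than illustrative, and the pre-treatment value of the outcome is not on it. That value is usually the strongest single predictor of the post-treatment value. Two things follow.

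First, if the arms start at different ABC levels, the post-only comparison counts part of that difference as treatment effect. Patient-level randomisation would limit such differences to chance. Here patients are placed by schedule, and two therapists per arm are too few to be relied on to balance caseloads. Eligibility is also broad (any disease, ages 60 to 89), so starting ABC may vary widely.

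Second, outcome variance that the baseline score would explain stays in the error term. This matters because a therapist-level comparison has only 4 − 2 = 2 degrees of freedom.

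The omission carries over to gait speed and, through the similar models, to the exploratory gait metrics.

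**Working it through.** **Inputs from Sample Size and Power Analysis:** N = 200, m = 50 patients per therapist, two therapists per arm, ICC 0.002 to 0.010, ABC SD 11 to 20, target 12 points, type 1 error 0.05. **Assumed, not in the article:** the pre-post correlation r, the pre-post slope and any actual imbalance.

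**1. Reproduce the article's power.** In SD units the variance of the arm difference is V = (1 + 49 × ICC)/50, which is the article's effective sample size restated. The noncentrality is λ = d/√V, tested two-sided on 2 df (critical value 4.303).
- ICC 0.002: V = 1.098/50 = 0.02196.
- d = 0.9: λ = 6.07, power 84.3%.
- d = 1.2: λ = 8.10, power 96.1%.

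Both match the printed 84.3% and 96.1%. The article's calculation therefore uses the raw SD with no baseline adjustment.

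**2. Size of a chance imbalance.** SE of the baseline difference = SD × √[(2/100)(1 + 49 × ICC)], taking the same ICC for baseline ABC.

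| SD | ICC 0.002 | ICC 0.010 |
|---|---|---|
| 11 | 1.63 | 1.90 |
| 20 | 2.96 | 3.45 |

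The 95% ranges run from ±3.2 points (1.96 × 1.63) to ±6.8 points (1.96 × 3.45).

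**3. What reaches the effect.** Carry-over = slope × imbalance. For an assumed 5-point imbalance and slope 0.7 this is 3.5 points, or 3.5/12 = 29% of the target. A simulation with no treatment effect (SD 15.5, 100 per arm, no clustering, 5-point imbalance) gave:
- r = 0.5: spurious effect 2.50 post-only and 0.00 with baseline ABC in the model; SE 2.19 and 1.94.
- r = 0.7: spurious effect 3.35 and −0.06; SE 2.17 and 1.56.

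Age, gender and pathology would absorb part of any imbalance, so these are maxima for the given slope.

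**4. Precision at SD 20 (d = 12/20 = 0.6).** Two assumptions bracket the gain:
- (a) all variance shrinks: V × (1 − r²);
- (b) only within-therapist variance shrinks: ICC + (1 − ICC)(1 − r²)/50.

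| r | ICC 0.002 (a) | ICC 0.002 (b) | ICC 0.010 (a) | ICC 0.010 (b) |
|---|---|---|---|---|
| 0 | 57.3% | 57.3% | 47.3% | 47.3% |
| 0.3 | 60.5% | 60.2% | 50.3% | 49.2% |
| 0.5 | 67.3% | 66.2% | 56.7% | 53.1% |
| 0.7 | 80.2% | 77.5% | 70.1% | 60.3% |
| 0.8 | 89.7% | 85.9% | 81.5% | 65.9% |

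**5. The other end of the SD range.** At SD 11, d = 12/11 = 1.09. Power without any covariate is 93.2% at ICC 0.002 and 86.4% at ICC 0.010, so there is little power left to gain.

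**6. A fairer starting point.** The r = 0 row has no covariates, but the planned model has three. If they explain an assumed 10% to 20% of the variance, V × 0.9 to V × 0.8 gives starting power of 61% to 65% at ICC 0.002 and 51% to 54% at ICC 0.010.

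**The case against.** **The list may not be meant as exhaustive.** The sentence naming the fixed effects mentions only treatment group, so a strict reading would drop age, gender and pathology too. The article also uses i.e. loosely: the Abstract and the Interventions section give different lists of feedback metrics. This lowers certainty about intent. It does not supply the missing term: the article names its covariates, and nothing in it indicates that baseline ABC is among them.

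**The gains depend on an r that the article does not give, and part of the variance is already explained.** This stands. It is why the gains are upper bounds and why case (b) and SD 11 are shown. Therapist variance that comes from how treatment is delivered cannot be explained by patients' starting scores, so the 90% and 82% figures should not be quoted alone.

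**No selection mechanism is shown.** This stands as well. Booking is described as blind to diagnosis, age and sex, and therapist experience is matched across arms. A reader might infer that the comparison is already known to be biased. The document supports only that it is unprotected: the absence of selection bias is stated there as an expectation. Chance imbalance alone is not bias over repetitions; it is the same loss as the lost precision, seen in one realised trial.

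**Gait speed.** A reader might infer a contradiction, because the text speaks of changes in gait speed while the model compares end levels. The article uses that word loosely for group differences in both power sections, and it states the ABC target as a difference at post-assessment. No separate error follows.

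**Conclusion.** The point holds. As written, the primary, secondary and exploratory models omit the baseline value of their own outcome, although it is collected. A starting difference between arms would pass into the ABC effect in proportion to the slope: up to 3.5 points under the assumed 5-point imbalance and slope 0.7, less what the planned covariates absorb.

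The precision loss is material at the upper end of the article's SD range and small at the lower end. At SD 20 and r of 0.5 to 0.8, the most that could be recovered takes power from 57% to 66-90% (ICC 0.002) or from 47% to 53-82% (ICC 0.010). This rests on the article's ICC range, on 2 df and on an assumed r.

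A reader might infer that the omission invalidates the trial, or that baseline adjustment would rescue it. Neither is supported. Two therapists per arm and non-random patient allocation remain limits either way, and one baseline score measured with error cannot remove all confounding. This is a free improvement to the analysis that should be made before the data are unblinded.

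**What to change.** Amend the Statistical Analysis text, and the analysis plan if there is one, so that:

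- the primary model includes baseline ABC as a fixed covariate;
- the gait-speed model includes the baseline speed of the same walk (casual pace with casual, faster pace with faster);
- each exploratory gait model includes the baseline value of its own metric;
- age, gender, pathology and the random therapist effect stay, with the covariates listed in the same sentence as treatment group so that the fixed effects are unambiguous.

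The cost is one covariate per model, from data already collected, and a change of wording. There is no change to visits, sample size or conduct. Make the change before unblinding, since adding the covariate afterwards would look data-driven. State beside it that the adjustment does not remedy having two therapists per arm or allocation by schedule.
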